### Interventions

Interventions will be administered by senior chartered physiotherapists in the four participating hospitals. All treating therapists will have attended two training sessions which will focus on the exercise and manual therapy interventions to ensure a standardised approach to treatment across the four trial centres.

The three components of the trial are as follows:

### Exercise therapy

Participants will attend six to eight 30 minute physiotherapy sessions over eight weeks. Each treatment will be administered on a one to one basis. The exercise intervention will incorporate flexibility and strengthening exercise using a semi-structured protocol, which provides guidance on exercise prescription and progression, but can be tailored to individual patient physical assessment findings. The content of the protocol is based on the findings of a questionnaire survey of the practice of Irish physiotherapists in the management of hip OA [19] and clinical guidelines for the management of hip and knee OA [21,24,54,55]. The focus of the strengthening programme is based on low load exercise, commencing in non weight bearing positions and progressing to functional positions [54]. The key target muscles are the gluteal muscles which are commonly atrophied in hip OA [56-58]. A range of exercises to address the various degrees of severity of hip OA will be available. Patients will also undertake a daily home exercise programme to supplement the clinic based treatment. They will complete an exercise log which will be reviewed by the treating therapist at each clinic attendance.

Each subject will be encouraged to undertake some form of aerobic exercise (such as walking, cycling, swimming) over the intervention period. They will be given written and verbal information on principles of aerobic conditioning such as pacing, gradually progressing intensity and time of exercise, doing 'little and often' and incorporating exercise into daily life. They will also be advised of cardiovascular warning symptoms/signs to be aware of, which may require review by a medical practitioner. Participants will be encouraged to achieve recommended aerobic exercise target of at least 30 minutes, five days a week [59].

### Exercise Therapy and Manual Therapy

Participants in this group will attend six to eight 45 minute sessions of physiotherapy over an eight week period. This will include 30 minutes of exercise therapy and 15 minutes of manual therapy. A choice of manual therapy techniques can be used which will be based on the pain/stiffness relationship as well as the movement restrictions of the affected hip. These will be ascertained by the blinded outcome assessor to ensure standardization and will be communicated to the treating therapists on a referral form. Treating therapists may choose from a list of manual therapy techniques based on Maitland [47], Mulligan [46], Cyriax [60] and other mobilization techniques such as muscle energy techniques [61] and proprioceptive neuromuscular facilitation (PNF)[62].

### Control Group (Waiting List Control)

Participants in the control group will continue to wait on the physiotherapy waiting list for an eight week period. On the 9^th ^week, they will complete a follow-up assessment with the blinded outcome assessor. They will then be re-randomised into one of the two intervention groups.

All groups will receive standardized written information on hip OA as recommended by clinical guidelines [22] including a standardised educational booklet entitled 'Osteoarthritis: helping you to understand osteoarthritis' and 'Osteoarthritis-Questions and Answers' published by Arthritis Ireland. This will ensure that education is not a confounding variable in the study.

All non-consenting and excluded participants will be treated as usual by the physiotherapy department of each trial centre. Participants will be asked to avoid all other forms of intervention for the duration of the RCT, apart from routine doctor care and analgesics. Participants with bilateral hip OA will receive treatment for both hips, but outcomes will be assessed on the worst affected hip only.

### Outcome Measures

Patients will be assessed at baseline, 9 weeks (end of treatment for the intervention groups) and 18 weeks (end of treatment for the control group) by the blinded assessor in the physiotherapy department of each hospital. Subjects in the control group will have an additional follow-up at 27 weeks (18 weeks post treatment) (Fig 1). Subjects and treating therapists cannot be blinded to treatment allocation due to the nature of the interventions.

**Figure 1 F1:**
[figure not shown]
**Flow of participants through the RCT**.

Standardised instruments with proven validity and reliability and in keeping with the core set of outcome measures of pain, physical function and global assessment as recommended by OMERACT III (Outcome measures in Rheumatology Group) [63] for use in osteoarthritis will be used. All outcomes will be measured at baseline, 9, and 18 weeks (and 27 weeks for the control group), unless otherwise stated.

The primary outcome measure will be:

### WOMAC (Western Ontario and McMaster Universities) Osteoarthritis Index Physical Function Subscale

The WOMAC is a multidimensional, self-administered health status instrument. It is available on both a 5-point Likert scale and a 100 mm visual analogue scale (VAS). In this study, the Likert version will be used. WOMAC consists of 24 questions regarding pain (scored 0–20), stiffness (scored 0–8) and physical function (scored 0–68). It has been shown to be a reliable, valid and responsive multidimensional outcome measure in patients with osteoarthritis of the hip or knee [64] and has been found to demonstrate superior responsiveness to the Lequesne Algofunctional Index [65]. Minimal perceptible clinical improvement has been found to be 9.3 mm on the physical function subscale on the WOMAC 100 mm normalised VAS [66].

Secondary Outcome Measures include:

### Global Assessment of Change (GAC)

Patient global assessment is one of the core domains which was recommended by OMERACT for evaluation in phase III trials in OA [63]. GAC comprises a single question which asks participants about the degree of change since their previous assessment and is therefore retrospective or transitional in nature. It functions as an external criterion to differentiate between changed and unchanged patients at the end of the study. It is subject to recall bias and can be heavily influenced by current status and patient satisfaction [67]. A 7-point Likert scale will be used ranging from 'very much worse' to 'very much better', with 'no change' located in the middle. The minimal clinically important difference of an average change of 0.5 on a 7-point scale has been found [68,69]. This will be measured at 9 and 18 weeks (and 27 weeks for the control group).

### Numerical Rating Scale (NRS) for Pain Severity

This is an 11-point scale that measures pain severity. Subjects will be asked to rate pain severity in the previous 24 hours with activity, at night and at rest. It is reliable, valid and preferable to a visual analogue scale in pain measurement, especially in an older population [70,71]. A change of approximately 2 points or 30% is considered to be clinically important [72].

### Short Form-36

This is a widely used well validated self-completed questionnaire that measures perceived health status and quality of life. It consists of eight multi-item scales measuring physical functioning (PF), bodily pain (BP), role limitations due to physical health problems (RP), general health (GH), vitality (V), social functioning (SF), role limitations due to emotional problems (RE) and mental health (MH)[73]. The scores on all subscales range from 0–100 with higher scores indicating better health status. A physical and mental health score can be derived from the items. The SF-36 has been used in other rehabilitation studies of hip OA [30,33,74].

### Hospital Anxiety and Depression Scale (HADS)

This self-report questionnaire measures mood disorder and is validated for use as a screening tool in the general population [75]. It contains 14 items, 7 relating to anxiety and 7 relating to depression, which are scored separately. A score of 0–7 indicates no anxiety or depression, 8–10 is borderline and 11–21 indicates the presence of anxiety or depression [76]. Due to the strong links between OA and psychological wellbeing [77,78], this outcome will be used to identify if anxiety or depression are confounders to treatment response and predictors of treatment outcome.

### International Physical Activity Questionnaire (short version)

This is a self-report questionnaire which asks participants to recall the amount of physical activity undertaken over the previous 7 days. It has been extensively validated across 12 countries for the measurement of physical activity in adults age 18–69 years [79].

### Physiotherapy Out-Patient Survey for patient satisfaction

This validated self-report questionnaire was specifically developed to measure patient satisfaction with physiotherapy in an outpatient setting. It measures dimensions of expectation of physiotherapy, communication, perceptions of the therapist, organization of treatment sessions, content of treatment session and outcome of treatment [80]. It will be completed at the 18 week follow-up assessment only.

### Pain Medication Usage (Pain Diary and Medication Quantification Scale (MQS))

Medication usage is a central management strategy in OA [15,20] and it is therefore important to measure the potential change in this usage over the course of the RCT. The MQS is an established, partially validated instrument that quantifies pain medication usage over a period of time. Each pain-related medication that participants are taking is given a score that is derived by multiplying the detriment weight of the drug and the relative daily dosage [81]. A single score is calculated that can be compared at different points in time and includes weighting for detrimental effects of the medication [82]. The daily dosage of pain medications will be measured using a medication diary which the participants will record over a 7 day period.

### Hip Range of Motion

Loss of range of motion (ROM) is a common clinical finding in hip OA and is associated with pain and disability [83]. Active range of motion will be measured on the affected hip. The movements of flexion, abduction, medial rotation and Thomas test will be measured using a universal goniometer. High test-retest reliability values for flexion, abduction and medial rotation have been reported (0.82, 0.86 and 0.90 respectively using the intraclass correlation co-efficient (ICC)) in subjects with hip OA [84]. A combined movement of flexion, abduction and external rotation (FABER) or the Patrick test will be measured using a measuring tape. This has been found to have a high test-retest reliability (ICC = 0.93) in healthy college-aged men [85] and a high correlation with radiographic changes in hip OA (Pearson's r = 0.54, p < 0.01). It is recommended for assessment of secondary endpoints in clinical trials [86].

### Physical Performance

Physical performance measures should be used in combination with self-report measures in the assessment of physical function [87]. In this study, two measures of physical performance will be used.

#### Repeated Sit to stand

This is one of a battery of measures used by Simmonds et al [88] to measure physical performance in subjects with chronic disorders. The task uses a standard armchair and requires the patient to stand from a sitting position and, as fast as possible, to return to the seated position 5 times. The task is repeated after a brief pause and the average time of 2 tasks is the resulting score. The average of 2 trials is necessary for acceptable reliability [89]. It has demonstrated excellent test-retest reliability (ICC = 0.83) and day to day retest reliability (ICC = 0.89) in 48 healthy pain-free subjects [89]. It has been used as an outcome measure in other OA studies [42,90].

#### 50 foot walk test

The 50 foot walk test is also one of the battery of physical performance tests used by Simmonds et al [88]. Subjects are asked to walk at their fastest speed along a premarked walk way of 25 feet, turn and return to the starting point. It has demonstrated test-retest reliability of ICC = 0.91 and day to day retest reliability of ICC = 0.65 in control subjects and ICC of 0.99 and 0.80 in low back pain subjects [89]. It has previously been used in a exercise-based osteoarthritis trials [91-93].

### Sample Size Considerations

The primary outcome measure-WOMAC physical function subscale- has been used to estimate the sample size required. The minimum clinically important difference (MCID) has been ascertained [66]. Using an MCID of 5.4 (SD = 11) on WOMAC Likert scale, with a significance level of 0.05 (2 tailed) and a power of 80%, it is estimated that 67 patients are required per group. To allow for 10% attrition at the 9 week follow-up, it is estimated that 74 patients will be required per group. However, as the waiting list control group will be re-randomised into 2 treatment groups after the 9 week follow-up, 50 patients per group will be required to give a total sample size of 150 patients.

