### Statistical Analyses

These will be blinded and will be performed in consultation with a statistician. Baseline and demographic data will be presented using descriptive statistics. Differences from baseline will be calculated for all primary and secondary outcomes. Mean differences, standard deviations and 95% confidence intervals will be calculated for all continuous outcomes. A longitudinal repeated measures design will be used to assess change from baseline and to make between group comparisons for the continuous outcome measures. Comparisons will be made between the 3 groups at the 9 week period. Participants in the control group will be analysed according to the intervention received after the 9 week follow-up and comparisons will be made between the 2 intervention groups at 18 weeks (both with and without the re-randomised control group subjects at the 18 week period). This will be done on an 'intention to treat' basis. Participants will be analysed in the intervention groups to which they were originally assigned and will include withdrawels and patients not treated by the assigned intervention. Missing data will be replaced using the last observation carried forward. Per-protocol analyses will also be performed by excluding patients with deviations from the treatment protocol.

At the 9 week and 18 week time points, continuous variables will be analysed using a mixed ANOVA model (with treatment as the between group factor and time as the repeated factor), or the non-parametric equivalent if non-normal distributions apply. Where significant differences occur, post-hoc comparisons will be conducted using Tukey's multiple comparison procedure. Differences in nominal/ordinal data will be analysed using the χ^2 ^test. A significance level of 0.05 will be set for any inferential statistics conducted.

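### The 80% power for 150 patients relies on pooled arms that first exist at week 18, while attrition is allowed for only to week 9; week-9 pairwise power is about 63–68%

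*Protocol article*

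**What the plan says.** All the inputs are in the protocol article, under Sample Size Considerations. The target difference and spread are given as "Using an MCID of 5.4 (SD = 11) on WOMAC Likert scale". The error rates are set in the words "with a significance level of 0.05 (2 tailed) and a power of 80" per cent, and the result is that "it is estimated that 67 patients are required per group". The attrition step follows: "To allow for 10% attrition at the 9 week follow-up, it is estimated that 74 patients will be required per group".

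The number enrolled is smaller. The reason given is "as the waiting list control group will be re-randomised into 2 treatment groups after the 9 week follow-up", from which the section concludes that "50 patients per group will be required to give a total sample size of 150 patients".

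Two other sections fix the timing. Outcome Measures makes week 9 the end of treatment for the original intervention groups and week 18 the end of treatment for the former controls, who also have a week-27 visit. Statistical Analyses compares the three groups at week 9. After that, "comparisons will be made between the 2 intervention groups at 18 weeks (both with and without the re-randomised control group subjects". The same section fills missing values by last observation carried forward and adds per-protocol analyses.

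**The concern.** The requirement of 67 evaluable per group is met only by adding half of the waiting-list group to each treatment arm. Those patients are re-randomised after week 9 and have no treated outcome until week 18. The attrition allowance is therefore dated to a visit at which the arms it should protect have not been formed, and nothing is allowed for loss between weeks 9 and 18.

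This has two consequences. The only comparison available at week 9 is between three groups of 50, well short of the number the plan says it needs. The comparison that has the numbers comes one period later, with almost no slack for further loss. A reader will take the paragraph to mean that 150 patients give 80% power with attrition covered, and it does not show this for either visit. A null result at week 9 could then be over-read as coming from an adequately powered comparison.

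**Working it through.** **Inputs from the article.** Difference 5.4, SD 11, two-sided alpha 0.05, power 80%, 10% attrition at week 9, three groups of 50, controls split between two arms after week 9.

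**Input assumed.** Loss in weeks 9–18 (call it *a*) is not stated. The article's own 10% is used as the central case, with 0–20% shown.

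**Method.** Two-sample t-test with *n* per arm, standardised difference d = 5.4/11 = 0.491, noncentrality d√(n/2), 2n − 2 degrees of freedom.

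**Step 1: the plan's figures.** Solving for 80% power gives n = 66.1, rounded up to 67, as stated. At n = 67 the power is 80.5%. Allowing for 10% loss, 66.1/0.9 = 73.4, which rounds up to 74, also as stated.

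**Step 2: pooled arms after one period of loss.** (50 + 25) × 0.9 = 67.5 per arm, power 80.8%. This is the plan's position if nobody is lost after week 9.

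**Step 3: week 9, not pooled.**

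| Patients per group | Pairwise power, unadjusted | Per pair with Tukey for three groups |
|---|---|---|
| 50 (no loss) | 68.1% | about 54% |
| 45 (10% lost) | 63.4% | about 49% |

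**Step 4: pooled at calendar week 18.** n = 75 × 0.9 × (1 − a).

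| Loss in weeks 9–18 (assumed) | n per arm | Power |
|---|---|---|
| 0% | 67.5 | 80.8% |
| 2% | 66.15 | 80.0% |
| 5% | 64.1 | 78.8% |
| 10% | 60.75 | 76.5% |
| 15% | 57.4 | 74.1% |
| 20% | 54.0 | 71.5% |

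The 10% row is 50 × 0.9 × 0.9 = 40.5 from the original arm plus 25 × 0.9 × 0.9 = 20.25 from the controls. Power crosses 80% where 67.5 × (1 − a) = 66.1, that is, at a loss of about 2%.

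**Step 5: a different pooling rule.** If each patient counts at the end of their own treatment (original arms at week 9, former controls at week 18), 10% loss per period gives 45 + 20.25 = 65.25 per arm and power 79.5%.

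**The case against.** A reader might infer that the pooled comparison simply fails to reach 80% power. The documents do not support that, for three reasons.

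- **The rate is not given.** The shortfall needs loss in weeks 9–18 above about 2%, and the article states no rate for that period. With no further loss, power is 80.8%.
- **The pooling rule matters.** Treatment ends at week 9 for the original arms and at week 18 for the former controls, so alignment on each patient's own end of treatment is a natural reading of the design. It gives 79.5%, in effect the planned 80%. On the other side, Statistical Analyses names 18 weeks for the pooled comparison, and no section states the aligned rule. The ambiguity is a reason to name the rule, not to assume the worse one.
- **Missing data are carried forward.** The intention-to-treat analysis retains withdrawals, so the nominal number stays between 72.5 per arm (controls lost before re-randomisation left out: 50 + 22.5) and 75, with nominal power of 83.5–84.8%. This stands as far as the head count goes. It does not show that the power is adequate: a control lost after re-randomisation would contribute a week-9 value recorded before any treatment, which carries no information on the treatment. By inflating for attrition, the plan itself treats withdrawals as lost information.

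A second tempting reading is that 74 is an inflation error, obtained as 67 × 1.1 = 73.7 where 67/0.9 = 74.4 would need 75. This does not stand. The article does not say how 74 was derived, and dividing the unrounded 66.1 by 0.9 gives the same 74. Nor would it matter, since 150 patients give 75 per pooled arm.

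None of these points touches the week-9 comparison. There the article's own requirement is 67 and the group size is 50.

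**Conclusion.** The point holds in a conditional form. The article's 80% belongs to pooled arms of about 75, while its attrition allowance belongs to a visit at which those arms do not exist.

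The clearest gap is at week 9. Pairwise power is 68.1% with 50 per group and 63.4% with 45, before any multiplicity adjustment, on the article's own difference, SD and attrition rate. No outside assumption is needed.

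At week 18 the 80% is not assured rather than refuted. The range is 80.8% with no further loss to 76.5% if the article's 10% recurs, a shortfall of about 3.5 points that rests on an assumed rate. It nearly disappears under own-end-of-treatment pooling. The calculations use a plain two-sample comparison of means, as the article's own figures imply. They do not model any effect of carried-forward values on the estimated difference.

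**What to change.** Rewrite the closing sentences of Sample Size Considerations so that they:

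1. name the comparison, visit and pooling rule to which the 80% applies (calendar week 18, or each patient's own end of treatment), and use the same rule in Statistical Analyses;
2. state the attrition expected cumulatively to that visit and the resulting power, about 76–81% for 0–10% loss in the second period;
3. state separately the pairwise power of the three-group week-9 comparison, about 63–68% before Tukey adjustment, and note that it is below the 80% target.

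The figures 67 and 74 can stay. The cost is a less favourable power statement, with no extra patients or visits. Should the sponsor instead wish to hold 67 evaluable per arm at calendar week 18 with 10% lost in each period, that would take 67/0.81 = 82.7, so 83 per arm or about 166 in total. That is an option, not a requirement of this point.

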Secondary analysis will be undertaken to assess the predictors of outcome at primary endpoint (9 weeks post treatment) in both intervention groups, using multiple regression analyses. A number of predictor variables such as age, gender, x-ray severity, baseline pain, physical function, mood, co-morbidities and treatment expectations will be measured. Analyses will be performed separately for exercise therapy, and combined exercise and manual therapy. Response variables will be change in WOMAC physical function score pre and post intervention (MCID> 5.4) and Global Assessment of Change. All predictors will be checked for collinearity. Univariate logistic regression will be performed on all potential predictors and those associated with the outcomes will be entered into the multivariate logistic regression model and backward regression will be performed. Variables with the lowest predictive value will be removed from the model if p > 0.05. Odds ratios and 95% confidence intervals will be calculated for all final predictors.

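### The 80% power does not apply to the 9-week three-group comparison: 50 per group gives 63–68% for one pair unadjusted, and about 49–54% with the planned Tukey procedure

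*Protocol article*

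**What the plan says.** Under Sample Size Considerations, the protocol article sizes the trial on its primary outcome: "The primary outcome measure-WOMAC physical function subscale- has been used to estimate the sample size required". The inputs are "Using an MCID of 5.4 (SD = 11) on WOMAC Likert scale", two-sided 0.05 and 80% power, and the result is that "it is estimated that 67 patients are required per group". An allowance of 10% for loss by the 9-week follow-up raises this to 74. The section then lowers recruitment because controls will be re-randomised after that follow-up: "50 patients per group will be required to give a total sample size of 150 patients".

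The Aim section makes the comparison of both interventions and the waiting list on physical function the primary aim. Statistical Analyses places it in time: "Comparisons will be made between the 3 groups at the 9 week period". After a significant result, "post-hoc comparisons will be conducted using Tukey's multiple comparison procedure". At 18 weeks only the two interventions are compared, once with and once without the re-randomised controls.

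**The concern.** The attrition allowance ties the 67 and 74 to week 9. The cut to 50 relies on patients who change arm only after week 9. When the three groups are compared, each holds at most the 50 it was allocated. The waiting list exists as a comparator only until then, so no contrast with it can ever exceed 50 per group.

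The calculation also assumes a single pairwise test at an unadjusted 0.05, whereas the plan tests pairs by Tukey's procedure, which is stricter.

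The section gives no power for 50 per group. A reader will therefore carry the only figure given, 80%, over to the primary aim. A non-significant 9-week contrast would then be read as evidence against a 5.4-point effect from a trial thought to have 80% power for it.

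**Working it through.** **Inputs.** Difference 5.4, SD 11, two-sided 0.05, 80% power, 10% attrition and 50 per group come from Sample Size Considerations. The Tukey procedure for three groups comes from Statistical Analyses. SD 11 is taken as the SD of the quantity analysed.

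**1. The plan's own figures.** Standardised difference = 5.4/11 = 0.491. Normal approximation: n = 2 × [11 × (1.960 + 0.842)/5.4]² = 65.1, rounded up to 66. With the noncentral t distribution, power is 79.9% at n = 66 and 80.5% at n = 67, so 67 reproduces. For attrition, 67 × 1.10 = 73.7, so 74 reproduces (67/0.9 = 74.4 would give 75, a trivial difference).

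**2. Where 50 per group comes from.** Half of 50 re-randomised controls go to each intervention: 50 + 25 = 75 recruited per arm, which covers 74. Then 75 × 0.9 = 67.5 evaluable, or about 80% power. This holds only for the two-intervention comparison that includes re-randomised controls.

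**3. One 9-week pair, unadjusted t-test.** Noncentrality = 5.4/(11 × √(2/n)).
- n = 45 (50 × 0.9): 5.4/2.319 = 2.329; power 63.4%.
- n = 50: 5.4/2.200 = 2.455; power 68.1%.

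**4. The same pair with Tukey.** The critical value is q(0.95; 3 groups, 3n − 3 df)/√2 = 2.37, against about 1.99 for the unadjusted test.
- n = 45: power 48.5%.
- n = 50: power 53.6%.
- n = 67: power 68.4%, so even the uncut number was not sized for Tukey.
- 80% power needs 86 analysed per group.

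Requiring a significant omnibus test first lowers the n = 45 and n = 50 figures by a further one or two points.

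**5. Difference detectable with 80% power.**

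| Analysed per group | Unadjusted t | Tukey |
|---|---|---|
| 45 | 6.6 | 7.5 |
| 50 | 6.2 | 7.1 |

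All four exceed the 5.4 points used for sizing.

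**6. Alternative procedure.** This is an omnibus F-test at 0.05 followed by unadjusted pairwise tests, simulated at a 5.4-point difference for one given pair.

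| Analysed per group | Third mean midway | Third mean equal to one of the pair |
|---|---|---|
| 45 | 51% | 57% |
| 50 | 56% | 62% |

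These are below the 63–68% of step 3 because the omnibus test must be passed first.

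**The case against.** **The 80% was meant for the pooled comparison, and the section gives the reason for the reduction openly.** This is probably right, and 50 + 25 = 75 fits it. A reader might infer that the protocol miscalculates, or that it expressly claims 80% for 50 per group at week 9. It does neither. What stands against it is that the section never says which comparison the 80% covers, and describes 50 per group simply as what is required.

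**Intention to treat with last observation carried forward keeps all 50 in the analysis.** This stands, and is why a range is given. At n = 50 the figures are still 68% and 54%, and that presumes carried-forward values do not dilute the effect.

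**SD 11 may be the SD of the final score, while the plan analyses change.** The document does not say. The SD of change would then be 11 × √(2(1 − r)), where r is the correlation between baseline and follow-up. With n = 45 and an unadjusted test, an assumed r = 0.5 changes nothing, r = 0.6 gives 73%, r = 0.7 gives about 84% (Tukey 74%), and r below 0.5 makes matters worse. So the absolute powers are conditional. The shortfall against the protocol's own 67 is not.

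**A near coin toss at a stated primary endpoint.** A reader might infer this, but it goes too far. About 50% holds for one given pair under Tukey. If both active arms are 5.4 points better than control, the chance that at least one differs significantly from it is about 65% (n = 45) to 70% (n = 50). The phrase "predictors of outcome at primary endpoint (9 weeks post treatment" belongs to the predictor analysis in the intervention groups and does not name the three-group comparison. The point rests on the primary aim and the 9-week attrition allowance.

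**The pooled comparison may fall short too.** That would need a second 10% loss among re-randomised controls, which the documents do not state. It is not part of this point.

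**Conclusion.** The reduction to 50 per group is justified by an event that comes too late for the comparison carrying the primary aim. The arithmetic behind 67 and 74 is sound. The fault is that the stated power does not match the 9-week design. About 80% holds only for exercise versus exercise plus manual therapy with the re-randomised controls included. It does not hold for any 9-week pair, any contrast with the waiting list, or the 18-week analysis that leaves those controls out.

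For one 9-week pair at 5.4 points, power is 63–68% unadjusted and about 49–54% with Tukey, for 45 to 50 analysed per group. These values assume that SD 11 applies to the analysed quantity and, at n = 50, that the full effect is kept. Tukey is itself a valid procedure; the problem is only that the sample size was not computed for it.

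**What to change.** Keep N = 150 and amend the sample-size paragraph.

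1. State that about 80% power applies only to the pooled two-intervention comparison including re-randomised controls.
2. State the 9-week pairwise power for the procedure actually used, with the number analysed and whether SD 11 refers to change or final score. With Tukey as planned and SD 11 for the analysed quantity, this is about 49–54%, with a detectable difference at 80% power of about 7.5 points (n = 45) or 7.1 points (n = 50).
3. Optionally, because there are exactly three groups, replace Tukey with an omnibus test at 0.05 followed by unadjusted pairwise tests. This also controls the familywise error, but gives up simultaneous confidence intervals. Its power should then be stated as about 51–57% (n = 45) or 56–62% (n = 50), depending on the pattern of means. The 63–68% of the ungated t-test must not be quoted for it.

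The cost is rewording and a less favourable power statement. No extra patients are needed.
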